## Abstract

**Introduction:**

Ventilator-associated pneumonia (VAP) is the most frequent healthcare-associated infection in intensive care units and is associated with high morbidity and mortality. Current diagnostic criteria lack specificity, leading to misclassification and unnecessary antibiotic use. Identifying patient subgroups with a common pathophysiological basis (pneumoclusters) may distinguish true VAP of varying aetiology and severity from non-infectious mimics, enabling more targeted therapy and improved antimicrobial stewardship.

**Methods and analysis:**

ClusterVAP is an exploratory, observational, prospective, multicentre cross-sectional study conducted in intensive care units across Sweden, France, Portugal, Denmark and the UK. Mechanically ventilated patients aged 18 years or older with newly developed clinical signs of lower respiratory tract infection will undergo bronchoalveolar lavage (BAL) or mini BAL sampling on clinical indication. Proteomic profiling using liquid chromatography tandem mass spectrometry will be performed on BAL supernatants. Unsupervised consensus clustering will define pneumoclusters, which will be characterised using clinical, microbiological and radiological data. 30-day outcomes, including mortality, ventilator-free days, antibiotic-free days, intensive care unit-free days and hospital-free days, will be compared across clusters to describe clinical trajectories. Candidate protein biomarkers for pragmatic cluster assignment will be derived using differential expression analysis.

**Ethics and dissemination:**

Ethical approval will be obtained at all participating sites. Deferred consent will be used where permitted, with subsequent patient or proxy consent according to local regulations. Results will be disseminated through peer-reviewed publications and scientific conferences.

**Trial registration number:**

NCT07245888.

WHAT IS ALREADY KNOWN ON THIS TOPICWHAT THIS STUDY ADDSClusterVAP will apply proteomic analysis of bronchoalveolar lavage samples to identify distinct patient subgroups, termed pneumoclusters and derive candidate biomarkers for pragmatic classification. This approach aims to improve diagnostic precision and provide insight into the underlying pathophysiology of VAP.HOW THIS STUDY MIGHT AFFECT RESEARCH, PRACTICE OR POLICYThe findings may inform future diagnostic algorithms, support antimicrobial stewardship and guide personalised treatment strategies in critically ill patients with suspected VAP.

## Introduction

 Ventilator-associated pneumonia (VAP) is the most frequent healthcare-associated infection in intensive care units (ICUs) and remains a major contributor to morbidity and mortality among critically ill patients.^1 2^ Reported incidence estimates vary widely, reflecting differences in case mix and diagnostic definitions, but VAP is consistently identified as a leading infectious complication of invasive mechanical ventilation and a key determinant of clinical outcomes and resource use in intensive care.^1 2^

Despite its clinical importance, diagnosing VAP with confidence remains challenging. Routine practice relies on a combination of non-specific clinical features, new or worsening radiographic infiltrates, blood leucocyte counts and culture results from lower airway samples, none of which in isolation provides adequate diagnostic certainty.^3 4^ In a systematic review, the presence of an infiltrate on chest radiography demonstrated high sensitivity but very low specificity, and combining radiographic findings with one or more clinical or laboratory criteria did not substantially improve specificity in most combinations.^5^ As a result, a considerable proportion of patients who meet consensus clinical criteria for VAP do not have bacterial pneumonia when assessed against lung biopsy histopathology.^5^ Estimates suggest that up to one half of clinically diagnosed cases may represent alternative conditions that mimic infection, including ventilator-induced lung injury, cardiogenic pulmonary oedema or acute respiratory distress due to non-infectious causes, each of which requires different management.^3^ A consequence of misclassification is unnecessary antibiotic exposure or missed opportunities to deliver appropriate treatment for the condition.

Biomarker research has not yet closed this evidence gap. Multiple candidate markers measured in lower respiratory tract specimens have been evaluated, but none has achieved a level of accuracy that would support widespread clinical use. In the most comprehensive syntheses to date, individual biomarkers such as soluble triggering receptor expressed on myeloid cells show only moderate sensitivity and specificity, and overall the evidence base does not support adoption of any single marker for routine VAP diagnosis.^6 7^ The lack of a reliable biomarker panel for bedside application reinforces the need for alternative strategies that can improve the separation of true infection from non-infectious mimics and that can also account for the biological heterogeneity within VAP itself.

A further challenge lies in the marked heterogeneity of the VAP construct. Patients who satisfy broad clinical definitions likely comprise biologically distinct subgroups that differ in aetiology, host response, disease stage and prognosis. Grouping such patients under a single label obscures meaningful differences that could guide treatment selection, antimicrobial stewardship and trial design. Molecular endotyping offers a principled route to disentangle this heterogeneity by identifying patient subgroups with shared pathophysiology and clinical trajectory. Bronchoalveolar lavage (BAL) provides a sample from the lower respiratory tract that captures local host responses within the infected compartment, and proteomic profiling can quantify a wide range of host proteins that reflect ongoing inflammatory and immune processes. Integrating this molecular information with carefully curated clinical, microbiological and radiological data creates an opportunity to define coherent and clinically useful subgroups, here termed pneumoclusters, within the broad VAP syndrome.

The ClusterVAP study is designed to address these needs. It is an exploratory, observational, prospective, multicentre cross-sectional investigation conducted in ICUs in several European countries. Proteome-driven, unsupervised consensus clustering will be used to endotype patients into ‘pneumoclusters’ with distinct pathophysiology and clinical trajectories. By focusing on endotyping at the site of disease using proteomics, ClusterVAP aims to advance the field in three ways. First, it seeks to improve diagnostic discrimination between true infection and non-infectious mimics within the population currently labelled as suspected VAP, thereby reducing unnecessary antibiotic exposure and facilitating appropriate alternative management. Second, it aims to identify more homogeneous subgroups with shared pathophysiology and prognosis, which could enable personalised treatment strategies and provide a framework for targeted interventional trials. Third, it intends to generate parsimonious biomarker panels that, after validation, could be translated into practical tools for bedside classification. The present protocol sets out the rationale and objectives of the ClusterVAP study and outlines how proteome-driven clustering integrated with routinely collected data may fill gaps left by existing diagnostic methods.

## Methods and analysis

### Study design

ClusterVAP is an exploratory, observational, prospective, multicentre cross-sectional study designed to identify biologically and clinically meaningful subgroups (pneumoclusters) among patients with suspected VAP. The study will be conducted in ICUs across Sweden, France, Portugal, Denmark and the UK. The protocol follows the Standard Protocol Items: Recommendations for Interventional Trials 2013 recommendations for interventional and observational studies (online supplemental file 1).^8^

### Patient and public involvement statement

No patients were involved in the development of this research.

### Study setting

Participating centres include ICUs in Sweden (Skåne University Hospital, University Hospital of Umeå, Karolinska University Hospital), France (CHU Limoges, Pitié Salpêtrière Hospital), Portugal (Hospital de São Francisco Xavier), Denmark (Rigshospitalet) and the UK (King’s College Hospital). These centres were selected to ensure diversity in patient populations and clinical practice while maintaining capacity for BAL sampling and adherence to harmonised protocols.

### Eligibility criteria

Adult patients (>18 years) who are admitted to an ICU, are receiving mechanical ventilation and from whom BAL or mini-BAL is collected on clinical indication for bacterial culture will be screened for inclusion and recruited to the study.

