### Inclusion criteria

New or worsening clinical signs compatible with lower respiratory tract infection within the preceding 24 hours, defined as the treating clinician’s suspicion plus at least one of:Body temperature >38°C or <36°C.Visually purulent tracheal secretions.Worsened oxygenation, demonstrated by the need to increase respiratory support to maintain the same partial pressure of oxygen/peripheral capillary oxygen saturation (SpO₂) target, defined as any of the following:Increase in fractional inspired oxygen (FiO₂) by ≥0.1 if baseline FiO₂ ≤0.5, or increase by ≥0.15 if baseline FiO₂ >0.5.Increase in positive end-expiratory pressure by ≥4 cmH₂O.Request for chest radiograph to investigate infection or new infiltrate.Initiation of antibiotic therapy targeting lower respiratory tract infection.Age 18 years or older at enrolment.

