### Exclusion criteria

BAL or mini-BAL collected solely for screening without suspicion of infection.Concurrent enrolment in the VAPmarkers study, which is reserved for external validation.

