### Outcomes

#### Primary outcome

Identification of pneumoclusters among patients with suspected VAP using unsupervised consensus clustering of BAL proteomic data alone and in combination with clinical and microbiological variables.

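### The eligibility criteria contain no ventilation-before-onset rule, so the clustered population is wider than the suspected VAP that the study names

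*Protocol article*

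**What the plan says.** The target population is stated under Study design and again under Primary outcome: "Identification of pneumoclusters among patients with suspected VAP". The Introduction places VAP in time by calling it a "leading infectious complication of invasive mechanical ventilation", which means it arises after ventilation has started.

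Who may enter is set out in three sections of the Protocol article:

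- **Eligibility criteria:** adult ICU patients who "are receiving mechanical ventilation and from whom BAL or mini-BAL is collected on clinical indication for bacterial culture".
- **Inclusion criteria:** "New or worsening clinical signs compatible with lower respiratory tract infection within the preceding 24 hours", made concrete as the treating clinician's suspicion plus at least one item from a list. The list includes abnormal temperature, purulent secretions, worsened oxygenation, a chest radiograph request and "Initiation of antibiotic therapy targeting lower respiratory tract infection".
- **Exclusion criteria:** two items only, "BAL or mini-BAL collected solely for screening without suspicion of infection" and "Concurrent enrolment in the VAPmarkers study, which is reserved for external validation".

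The Abstract describes entry a little more narrowly, as patients "with newly developed clinical signs of lower respiratory tract infection".

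**The concern.** What separates VAP from other pneumonia in a ventilated patient is whether the infection arose on the ventilator or was already there when ventilation began. The printed criteria do not ask this. The suspicion they require is of lower respiratory tract infection, not of VAP, so the clinician's judgement does not fill the gap.

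This matters more here than in a study with a fixed contrast, because the primary outcome is an unsupervised partition: whoever is enrolled shapes the clusters. If pneumonia that led to ventilation is mixed with pneumonia acquired on it, part of the proteomic structure could restate a distinction that the intubation time already gives. Biomarkers chosen for cluster assignment would inherit it. The 30-day comparisons (mortality and days free of ventilation, antibiotics, ICU and hospital) could also partly reflect where patients stand in their illness at sampling.

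**Working it through.** No formula applies to the claim itself, so the check is a reading of the criteria against one test patient: an adult intubated a few hours ago because of community-acquired pneumonia, with fever and antibiotics started in the last day, and a BAL sent for culture.

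| Requirement | Section | Test patient |
|---|---|---|
| Adult, in ICU | Eligibility criteria | met |
| Currently on mechanical ventilation | Eligibility criteria | met |
| BAL or mini-BAL taken for clinical reasons | Eligibility criteria | met |
| Clinician suspects lower respiratory tract infection | Inclusion criteria | met |
| At least one listed sign, new or worse within 24 hours | Inclusion criteria | met (fever; antibiotics started) |
| Screening sample without suspicion | Exclusion criteria | does not apply |
| Enrolled in VAPmarkers | Exclusion criteria | does not apply |

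The patient enters, yet the pneumonia is not a complication of ventilation in the Introduction's sense.

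**Does the word worsening create the gap?** Delete it and repeat the check. The fever and the antibiotic start are both new within 24 hours, so the patient still enters. The Abstract's narrower phrase would not keep the patient out either. The gap is the missing link between onset and ventilation.

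**Does a planned analysis separate the two groups?** The sensitivity analyses at the end of Statistical analysis are:

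- a stricter protein-completeness threshold: unrelated to onset;
- restriction to microbiologically confirmed pneumonia: keeps culture-positive patients intubated for pneumonia;
- the largest site alone: unrelated to onset;
- time from collection to freezing: unrelated to onset.

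None uses time on the ventilator before onset.

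**Scale, for orientation only.** The Sample size section gives 400 patients and four to six expected clusters, with no calculation to reproduce. If clusters were equal, which the article does not say, the average size would be 400/6 = 67 to 400/4 = 100. The share of patients with pneumonia before intubation is not given. Assumed shares of 10%, 20% and 30% would be 400 × 0.10 = 40, 400 × 0.20 = 80 and 400 × 0.30 = 120 patients. These are head-counts under an assumption. They do not show whether such patients would separate in the proteomic data.

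**The case against.** The strongest reply is that broad entry is deliberate. The study is exploratory and observational, tests no confirmatory hypothesis, and sets out to take a heterogeneous clinical population apart. Clusters will be described afterwards with clinical, microbiological and radiological features, so a cluster driven by early pneumonia could be recognised then. Intubation time may well be on the full case report form: Data collection and management mentions baseline clinical data without listing fields, and an article need not list them. The criteria also point to an invasively ventilated setting through tracheal secretions and end-expiratory pressure, even if they do not formally require it.

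Much of this stands. It lowers the severity, and it means the article cannot be said to omit intubation time from data collection. It does not close the gap. The heterogeneity that the Abstract and Introduction set out to resolve lies between true VAP of different kinds and non-infectious mimics. Pneumonia that caused the intubation is neither: it is infectious, but it is not VAP. Description after the fact can label such a cluster, but it cannot undo the influence of these patients on the partition. Eligibility is also not something an analysis plan or the condensing of an article would normally supply, since the article prints itemised lists down to increments of inspired oxygen.

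A reader might go further and infer three things that the documents do not support:

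- That these patients will form a cluster of their own. This is plausible but undemonstrated, and a head-count similar to an average cluster is no evidence for it.
- That accepting worsening signs is what lets them in. The check above shows otherwise.
- That the primary outcome becomes uninterpretable. A recorded time and reason for intubation would allow restriction or stratification.

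**Conclusion.** The concern holds as a mismatch between the written criteria and the named population. As printed, the study clusters ventilated patients with suspected lower respiratory tract infection, which includes but is wider than suspected VAP. Clusters and their outcome differences could partly reflect pneumonia before versus after intubation, and no prespecified analysis would show how far.

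The size of the effect cannot be derived from the documents. It depends on the unknown share of such patients and on how differently their proteomes behave. The conclusion that they can enter rests on the printed criteria alone and needs neither assumption. It does presuppose that the full protocol adds no onset rule that the article leaves out. For an exploratory study with an inexpensive remedy, I rate this moderate.

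**What to change.** Reconcile the eligibility text with the suspected-VAP label, in one of these ways:

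1. **Preferred.** Keep screening broad. Capture time of intubation and reason for intubation, if they are not already on the form. Prespecify the primary clustering set as patients whose signs began after a period of invasive ventilation, and analyse the others as a separate stratum. State how onset is dated when the qualifying sign is a worsening one.
2. **At the least.** Add to the sensitivity analyses a repeat of the clustering restricted to that set, and describe the main clusters by time from intubation to onset and by reason for intubation.

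The documents give no duration, so the length of the period is for the sponsor to choose and justify. The Abstract's description of the qualifying signs should be aligned with the Inclusion criteria at the same time.

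The cost is a sentence defining the analysis set and at most two form fields. The downside is a somewhat smaller primary set than 400, or longer recruitment if 400 is to be kept for that set. The fields should be captured from the start, because timing may be hard to recover later.

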### Inclusion criteria

New or worsening clinical signs compatible with lower respiratory tract infection within the preceding 24 hours, defined as the treating clinician’s suspicion plus at least one of:Body temperature >38°C or <36°C.Visually purulent tracheal secretions.Worsened oxygenation, demonstrated by the need to increase respiratory support to maintain the same partial pressure of oxygen/peripheral capillary oxygen saturation (SpO₂) target, defined as any of the following:Increase in fractional inspired oxygen (FiO₂) by ≥0.1 if baseline FiO₂ ≤0.5, or increase by ≥0.15 if baseline FiO₂ >0.5.Increase in positive end-expiratory pressure by ≥4 cmH₂O.Request for chest radiograph to investigate infection or new infiltrate.Initiation of antibiotic therapy targeting lower respiratory tract infection.Age 18 years or older at enrolment.

### Exclusion criteria

BAL or mini-BAL collected solely for screening without suspicion of infection.Concurrent enrolment in the VAPmarkers study, which is reserved for external validation.

### Consent

Because patients eligible for inclusion are critically ill and typically lack decision-making capacity at the time of sampling, and the risk of harm or discomfort anticipated by participation in the study infers minimal risk, consent will be waived or deferred where permitted by local legislation and approved by relevant review boards. If deferred, written informed consent will be sought from the patient; if this is not possible, consent will be obtained from a legally authorised representative in accordance with site specific requirements. All consent procedures will be documented, and any additional provisions for the use of biological specimens and associated data will comply with national and institutional policies.

### Sampling and laboratory procedures

BAL or mini-BAL will be performed according to local standard of care using either bronchoscopy or an unguided catheter. The sample will be split for routine microbiology and for study-specific proteomic analysis using liquid chromatography tandem mass spectrometry (LC MS/MS). After routine microbiological analysis, the remaining supernatant will be centrifuged at 2000 g for 5 min, aliquoted into sterile nuclease-free vials (target 2 mL, minimum 1 mL) and stored at −20°C to −80°C. The time from sample collection to freezing should be kept to a minimum and must not exceed 12 hours. Samples will be shipped on dry ice in batches to Lund University for proteomic analysis.

Proteomic profiling will be performed using LC MS/MS with data independent acquisition. Quality control will include pooled reference samples and replicate injections. Total protein concentration will be measured by a colourimetric assay, and selected proteins will be quantified by ELISA.

Biological samples will be stored under controlled conditions for up to 10 years to allow confirmatory analyses, after which they will be destroyed.

### Outcomes

#### Primary outcome

Identification of pneumoclusters among patients with suspected VAP using unsupervised consensus clustering of BAL proteomic data alone and in combination with clinical and microbiological variables.

#### Secondary outcomes

Comparison of 30-day clinical outcomes across clusters, including: All-cause mortality, ventilator-free days, antibiotic-free days, ICU-free days and hospital-free days.Derivation of candidate protein biomarkers for pragmatic cluster assignment.

### Sample size

As an exploratory clustering study, a formal power calculation is not applicable. Based on anticipated heterogeneity and the expectation of four to six major clusters, the target sample size is 400 patients. This number balances scientific aims with the resource-intensive nature of proteomic analysis and is considered sufficient to identify clinically meaningful clusters while allowing for internal validation.

### Data collection and management

Data will be recorded in electronic case report forms hosted in REDCap at Lund University, with access restricted to authorised study personnel. The first form will capture enrolment and sampling details; the second, completed at least 30 days after enrolment, will include demographics, baseline clinical data, microbiology results and outcomes. Built-in range checks and logic controls will support data quality. All data will be pseudonymised using site-specific sequential codes, with re-identification keys stored securely at each site.

### Statistical analysis

Proteome-driven unsupervised consensus clustering will be used to discover pneumoclusters that are then described using clinical, microbiological and radiological features. Proteomic data processing will include analysing raw DIA files (dia-PASEF on Bruker timsTOF) with DIA-NN (V.1.8.1) against the UniProt human reference proteome. False discovery rate (FDR) will be controlled at 1% at both precursor and protein levels using a target–decoy strategy. Proteins with >70% missing values across all samples will be removed. Retention-time–dependent normalisation followed by median normalisation will be applied.

Unsupervised consensus clustering with resampling will be applied to define stable clusters, with cluster number determined by cumulative distribution function and silhouette width. Differential abundance will be assessed using limma. Multiple testing will be controlled with Benjamini-Hochberg correction and proteins will be considered significant at adjusted p<0.05 and |log₂ fold-change|>1.5. Gene set enrichment will be performed using clusterProfiler against Gene Ontology and Reactome collections with FDR<0.01.

30-day outcomes, including mortality and days free of ventilation, intensive care, hospitalisation and antibiotics, will be compared across clusters to characterise distinct clinical trajectories. Missing proteomic data will lead to exclusion from clustering; missing clinical variables will be handled by complete case analysis for relevant comparisons.

Candidate protein biomarkers that enable pragmatic assignment to clusters will be derived using differential expression methods and feature selection methods, with the intention of informing future validation with receiver operating characteristic (ROC) curves in separate patient cohorts and, ultimately, clinical application. Biomarker validation is planned in an independent external prospective observational study (VAPmarkers; ClinicalTrials.gov: NCT05117125). Validation will rely on targeted quantification of selected proteins using ELISA or equivalent immunoassays, and diagnostic and prognostic performance will be assessed using ROC curves.

To evaluate the robustness of our findings, we will perform several prespecified sensitivity analyses. First, we will repeat the clustering and differential abundance analyses using a stricter protein-completeness threshold (requiring ≥90% quantification across samples) to determine whether pneumocluster structure is sensitive to missingness. We will also reassess key analyses restricted to microbiology-confirmed cases with pneumonia in order to evaluate the effect of potential misclassification. In addition, we will repeat the unsupervised clustering using data from the largest enrolling site alone to examine whether cluster formation persists independently of between-centre heterogeneity. Finally, to assess potential influence of preanalytical handling, we will analyse the relationship between time from collection to freezing and proteomic structure, and repeat the main analyses after excluding samples with the longest delays to ensure that freezing time does not bias cluster allocation or biomarker identification.

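### The stated rule for the number of clusters can only rank two or more, so finding pneumoclusters is not in itself evidence of discrete subgroups

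*Protocol article*

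**What the plan says.** The Statistical analysis section of the protocol article gives the method and the rule for the number of clusters, k: "Unsupervised consensus clustering with resampling will be applied to define stable clusters", "with cluster number determined by cumulative distribution function and silhouette width". It gives no numeric meaning for stable.

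The primary outcome is "Identification of pneumoclusters among patients with suspected VAP using unsupervised consensus clustering of BAL proteomic data alone", and also with clinical and microbiological variables added. The Sample size section starts from "the expectation of four to six major clusters" and sets a target of 400 patients; it states that "a formal power calculation is not applicable".

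The sensitivity analyses at the end of the Statistical analysis section use a stricter protein-completeness threshold, microbiology-confirmed cases only, the largest site only ("to examine whether cluster formation persists independently of between-centre heterogeneity"), and an examination of freezing delay with the longest delays excluded. The planned external study validates biomarkers by ROC curves.

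**The concern.** The primary outcome concerns whether subgroups exist and how many there are. A rule that chooses only among two, three, four or more clusters answers how many while assuming that they exist. If patients with suspected VAP lie along a smooth gradient of host response, the procedure will still cut it into groups. Resampling may place the cut at nearly the same point each time, so the groups look stable.

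The later results are conditional on those labels: the 30-day outcome comparisons, differential abundance, enrichment and the candidate biomarkers for cluster assignment. Groups cut from a severity gradient would be expected to differ in mortality and in many proteins, so such differences would not show that the groups are discrete.

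**Working it through.** The plan has no figure to reproduce here: 400 is given as a judgement, without alpha, power or effect size. The check therefore has three parts.

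**1. What the two indices can return.**

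- Silhouette for patient i is s(i) = (b − a) / max(a, b). Here a is the mean distance to patients in the same cluster and b is the smallest mean distance to another cluster. At k = 1 there is no other cluster, so b and s do not exist (numerically, nan).
- The consensus value for a pair is the number of resamples in which both fall in the same cluster, divided by the number in which both are sampled. At k = 1 it equals 1 for every pair in any data set. The CDF is then a single step at 1 and says nothing about the data, so comparison starts at k = 2.

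This part follows from the definitions and needs no simulation assumptions.

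**2. Whether another stated analysis supplies the missing comparison.** The completeness and largest-site analyses repeat the clustering. The long-delay exclusion repeats the main analyses, and the microbiology-confirmed analysis reassesses key analyses in a subset. If the same rule is used in the largest site, at least two clusters must form there too. Whether they resemble the main ones is informative, but the fact that clusters form is not. The external validation concerns biomarkers.

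**3. How a continuum would look.** Assumptions not in the documents: 400 patients, 200 features, k-means base clusterer, 80% subsampling, 40 resamples, k from 2 to 8. The CDF criterion was read as the lowest proportion of ambiguous pairs (PAC, consensus strictly between 0.1 and 0.9). The last two columns are means over data sets of the best value across k.

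| Simulated truth | Data sets | k by silhouette | k by PAC | Consensus silhouette | PAC |
|---|---|---|---|---|---|
| Pure noise | 6 | 2 or 3 | 8 | 0.10 | 0.88 |
| One continuous axis | 12 | 2 in all | 2 (11), 3 (1) | 0.96 | 0.10 |
| Three continuous factors, unequal (1, 0.8, 0.6) | 12 | 2 (11), 3 (1) | 2 (11), 8 (1) | 0.92 | 0.16 |
| Five true clusters | 6 | 5 in all | 5 (3), 6 (3) | 0.96 | 0.07 |

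On protein-data distances instead of consensus distances, the best silhouettes were 0.01, 0.25, 0.19 and 0.27 in the same order. One axis is again close to five true clusters.

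Further runs at 400 patients varied the settings:

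- 600 features, one axis, k = 2: consensus silhouette 0.94 to 0.97, PAC 0.06 to 0.11.
- 600 features, five true clusters, k = 5: 0.96 to 0.98, PAC 0.02 to 0.16.
- 600 features, three unequal gradients: 0.92 to 0.97. Three equal gradients: 0.57 to 0.89.
- 1,500 features, three equal gradients with 40% of variance, k = 2: 0.66 to 0.77, PAC 0.53 to 0.66, which is visibly unstable.

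**4. Whether a reference population repairs the rule.** The best silhouette over k = 2 to 8 (k-means on the 200-feature data) was compared with 19 data sets drawn from one Gaussian with the same covariance. Clusters were declared only if the observed value exceeded all 19, a level of 1/(19 + 1) = 0.05.

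| Truth | Rule without reference gives k ≥ 2 | Clusters declared with reference |
|---|---|---|
| One axis | 20/20 | 1/20 |
| Three factors | 20/20 | 0/20 |
| Five true clusters | 8/8 | 8/8 |

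Without the reference, the silhouette rule gave clusters in 20 + 20 + 8 = 48 of 48 data sets.

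**The case against.** **Detail left to the analysis plan.** The range of k, stability thresholds and reporting rules commonly sit in a full protocol or SAP, and the article promises the protocol and code with the main report. That stands for those details. It does not settle this point, because the article itself names the criteria that determine k, and neither can select one cluster.

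**A false finding is not certain.** A reader might infer that false clusters are guaranteed whenever the truth is one population. The documents do not support that. An index having its maximum at some k of two or more differs from the investigators declaring subgroups. Both indices are graded, stability is a stated aim, and pure noise (0.10; PAC 0.88) would look poor. Several equally strong gradients may also look poor. The simulated continua mostly gave k of 2 or 3, which would sit awkwardly with the four to six expected. These safeguards depend on judgement, however, as no threshold is stated, and a one-axis continuum would pass by eye.

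**The clusters would still carry information.** A reader might also infer that any pneumoclusters found carry no evidence at all. That goes too far. The 30-day outcomes are not used in the protein-only clustering, and re-clustering in the largest site is informative about reproducibility. What these analyses cannot do is separate a divided gradient from discrete groups.

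**The study is exploratory.** It is observational, with no alpha or power, and biomarkers go to external validation before clinical use. This lowers the severity; it does not give the primary outcome a possible negative result.

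**Conclusion.** The concern holds in this form: the rule as stated always returns at least two clusters, and no stated analysis tests the partition against a single continuous population. The first part is a matter of definition.

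The size of the problem depends on the unknown structure of the data. If one axis dominates, a continuum is nearly indistinguishable from real clusters on these indices (consensus silhouette about 0.94 to 0.97 against 0.96 to 0.98). With several equally strong gradients the value is about 0.6 to 0.9 and the instability may be noticed. These figures rest on assumed k-means clustering, subsampling settings, feature counts and Gaussian gradients, none of which the article gives.

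This should be fixed before clustering begins. It does not invalidate an exploratory study, since a divided gradient remains a usable description if it is labelled as one.

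**What to change.** Amend the Statistical analysis section as follows.

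1. State that no discrete clusters is an admissible result for the primary outcome.
2. Prespecify one overall statistic, for example the maximum silhouette over a stated range of k, on a stated distance. A separate test at each k would raise the overall error above 5%.
3. Compare it with its distribution in at least 100 reference data sets passed through the same pipeline. Simulate them from one population with the same covariance and the observed marginal distributions. With more proteins than patients, the covariance must be regularised or based on principal components. Matching the marginals matters because skewed protein data could exceed a purely Gaussian reference without any clusters.
4. Claim discrete pneumoclusters only if the observed value exceeds the 95th percentile. Otherwise, report the partition as a descriptive division of a continuous gradient.
5. Keep the CDF and silhouette for choosing among two or more clusters, and name one as deciding.

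The check in step 4 of the working used a simpler version (19 Gaussian references, 200 features, Gaussian continua), so it shows feasibility rather than the exact error rate of this rule. The change needs no new patients or samples. It costs some specification work and computing time, and the study may report no discrete clusters or miss weakly separated ones.
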